***Intermediate reviews and analyses:***

Patient medical data will be collected from the facilities at three points over the 10 month study period. At each point, it will be transferred to the CDC for analysis. In addition, the PI will track the progress of the study and report this information to the CDC on a monthly basis, or more frequently.

***Limitations of study:***

This study is intended to provide specific data that will be used to refine the video intervention. These study results are not meant to be applicable to other interventions. A major limitation of the patient medical data part of the study is that it will not demonstrate conclusively that outcomes observed are due to exposure to the video. Available funding only allows 10 months of data collection, not 12 months as required by core indicators for the outcomes. Also there is no way to measure actual video exposure or dosage. With this study design, we can only observe associations between outcomes and presumed exposure. Limitations of the observational data are that observations will be conducted on only one day so data redundancy may not be reached, and the observer cannot be certain that the apparent demographics of the patients are 100% accurate or that patients are actually engaged with the video. Despite this, we believe the observations will allow for meaningful information that can be used to improve the video.

***E. HANDLING OF UNEXPECTED FINDINGS AND ADVERSE EVENTS***

***Response to new or unexpected findings and to changes in the study environment:***
New or unexpected findings will not be identified until data are analyzed at the end of the 10-month beta-test. All findings will inform the video refinement and improvement to increase its effectiveness among HIV-positive persons in medical care settings.

The PI will communicate by phone or email at least monthly with facility managers to deal with any changes which might arise in the study environment. Specifically, the PI will ensure that there are no issues with regard to playing the video or collection of patient data from the EMR. During the monthly communication, he will check that the video has been played each day and that the video is looping at a minimum of 20-minute intervals. Facility managers will be asked to report to the PI immediately if there are any issues, such as equipment malfunctioning or missing equipment. In the event of malfunctioning or missing equipment, the PI will work with the facility manager to replace the equipment. If there are changes in the EMR software used at the facilities, the PI and data manager will work with the facilities’ EMR data staff to make sure that all of the required variables continue to be collected.

***Identifying, managing, and reporting adverse events or incidents:***

Because the study involves using pre-existing, de-identified medical data and unobtrusive observation in public waiting rooms, we believe that the possibility of adverse events is minimal. However, if an adverse event occurs, such as the inadvertent placing of PII on the encrypted USB drive by the facility’s staff, this would be reported to CDC within 1 hour of discovery. The facility staff person responsible for placing the PII on the USB drive would be re-trained to de-identify and remove PII from the patient medical data.

***F. SHARING STUDY RESULTS***

***Anticipated products or inventions resulting from the study and their use:***

This study will result in a refined waiting room video for HIV/AIDS treatment facility waiting rooms that will be used as an intervention to improve HIV treatment adherence, retention in care, and sexual risk reduction for individuals with HIV. After refinement, the video will be available for use by HIV/AIDS treatment facilities across the US.

***Disseminating results to public:***

A data sharing plan will be developed explaining how and when CDC will make project data publically available. Publication guidelines and agreements will be developed as well.

**IV. HUMAN SUBJECTS PROTECTIONS**

***A. INFORMED CONSENT***

***Procedures for implementing and documenting informed consent:***

A waiver of written informed consent is being requested because the research presents no more than minimal risk to the subjects and because no personal identifying information will be collected. The patient medical data will be extracted from existing medical record data from the treatment facilities’ EMRs and de-identified by a computer algorithm. Furthermore, the systematic observations will take place unobtrusively in a public location.

***B. RISKS & BENEFITS***

***Description of risks (physical, social, psychological, economic, other) to the individual or group. Include methods to minimize risks:***

The proposed research presents no more than minimal risk to subjects. Some waiting room patients may feel uncomfortable if they notice that they are being observed. However, the trained observer will make every effort to be as unobtrusive as possible and will not approach any waiting room patients. In addition, there is slight risk that some PII could end up in the data on the encrypted USB drive. This is unlikely, however, as the medical data will be de-identified by treatment facility staff before it is transferred to the encrypted USB drive, and then checked once more after this transfer. The fact that the USB drive itself is encrypted adds another layer of protection. Upon receiving the USB drive, the data manager will immediately check the data for PII before loading the data onto the secure laptop. If any PII was present, the data manager would report this to the CDC within 1 hour of discovery.

***Description of anticipated benefits to the research participant*:**

The study will not enroll research participants. We anticipate that the beta-test version of the video will result in improved outcomes for patients in the waiting room when the video is shown with regard to HIV treatment adherence, retention in care, and sexual risk reduction. Consequently, this will lead to better health outcomes for patients with HIV and their sex partners.

***Description of the potential risks to anticipated benefit ratio:***

No participants will be enrolled in the study; however, patients will be exposed to the intervention video. Benefits of exposure to the video are increased likelihood of improved adherence to medication and retention in medical care and decreased likelihood of transmitting HIV to sex partners. This greatly outweighs the risk of becoming uncomfortable due to sensitive topics portrayed in the video. We believe that the overall risk classification for this study is minimal risk. As the final video will be made available for HIV/AIDS treatment facilities across the US, it has the potential for widespread improvement of the health of many people with HIV, as well as for their sex partners. We therefore believe that the potential risks of this investigation are greatly outweighed by the anticipated benefits.

***C. PRIVACY & CONFIDENTIALITY***

***Provisions for protecting privacy/confidentiality***

Patient medical data will be de-identified by treatment facility staff before it is transferred to the encrypted USB drive, and then checked once more after this transfer. The fact that the USB drive itself is encrypted adds another layer of protection. Upon receiving the USB drive, the data manager will immediately check the data for PII before loading the data onto the secure laptop. If any PII was present, the data manager would report this to the CDC within 1 hour of discovery. After the data manager confirms the data contain no PII, she will immediately transfer it to a secure laptop, which is not connected to the internet (the wireless card will be removed). This laptop will be stored in a locked cabinet in her office, which is also locked when the data manager is not inside. The laptop will be password protected, and the password will be changed every 60 days. The data manager and the facility staff responsible for de-identifying the data will be required to sign a Rules of Behavior document which is required by the CDC to protect against any identification of study participants. No identifying data will be published or released outside of the project.

***Statement about need or lack of need for Assurance or Certificate of Confidentiality:***

We do not anticipate that any formal confidentiality protections will be needed for this research, as we will not be enrolling any participants, and the study will consist of collecting de-identified patient medical data and unobtrusive observational data in public waiting rooms.

***Emergency care:***

As no patients will be enrolled in this study, there is no risk of an emergency as a result of this study. If an emergency occurred with a patient while they were in the waiting room, they would be in a clinic or HIV case-management office where staff are trained to deal with health emergencies.

***Description and justification of reimbursements or incentives that will be used:***

No participants will be enrolled; therefore, no reimbursements or incentives will be used.

***Notifying participants of their individual results:***

No participants will be enrolled; therefore, there will be no individual results.

***Notifying participants of study findings:***

No participants will be enrolled; therefore, there will be no one to be offered the option of receiving overall study findings.

**VI. APPENDIX MATERIALS**

**APPENDIX 1: RULES OF BEHAVIOR DOCUMENT**

**APPENDIX 2: OBSERVATION PROTOCOL**

**APPENDIX 3: OBSERVATION INSTRUMENT**

**Appendix 1: Rules of Behavior Document**

Prevention with Positives-Antiretroviral Therapy (PWP-ART Video) Rules of Behavior (RoB)

All users collecting, storing or transferring PWP-ART Video study participant information must read these rules and sign the accompanying acknowledgement form. This acknowledgement must be signed annually to reaffirm knowledge of, and agreement to adhere to the PWP-ART Video RoB.

These rules cannot account for every possible situation. Therefore, personnel shall use their best judgment and highest ethical standards to guide their actions.

I assert my understanding that:

- Collection, storage, and transfer of Sensitive Information (SI) must comply with Federal Government, Department of Health and Human Services (HHS), and Centers for Disease Control and Prevention (CDC) policies and standards, and with applicable laws;
- SI for the purpose of the PWP-ART Video study includes patient demographic, HIV status, and laboratory test result information for study participants;
- Unauthorized access to information is prohibited, Authorized users shall not share or loan their credentials with any individual in order to allow that individual to gain access to the PWP-ART Video Laptop; and
- Users must prevent unauthorized disclosure of SI, Personal Health Information (PHI), or Personally Identifiable Information (PII) by following the procedures listed in the PWP-ART Video RoB.

For individuals with electronic access to the PWP-ART Video Laptop:

I shall:

- Only connect the PWP-ART Video Laptop to the internet once to initially install the system and analysis software required for the Laptop, after which no further connection to the internet will be allowed without written permission from the NCHHSTP ISSO [name] and the wireless card will be removed from the Laptop to prevent inadvertent connection to the internet;
- Update software on the PWP-ART Laptop that is necessary to perform job functions by using software disks purchased off-the-shelf; If such disks are not available, obtain authorization from CDC NCHHSTP ISSO, [name], before downloading software from the internet;
- Log-off or lock the PWP-ART Video Laptop and lock the office door when leaving it unattended;
- Store the CDC issued encrypted USB devices in a locked drawer or cabinet when not in use to prevent loss;
- Use a separate Administrative and User password for access to the Administrative functions of the Laptop and regular user functions.
- Create a password that complies with the following minimum requirements:
  - Minimum of 8 characters
  - Use at least one each of 3 of the 4 types of characters, Upper Case Letter, Lower Case Letter, Number, and Special Character
  - Change Administrative and User passwords at least every 60 days and set 2-week reminders on the Laptop;
  - Send report verifying password changes to the CDC Project Officer (Contracting Officer’s Representative)
- Use Federal Information Processing Standards (FIPS) 140-2 full disk encryption on the Laptop such as Symantec Drive Encryption (PGP Whole Disk Encryption)
- Use only CDC issued encrypted USB devices to transfer data to or from the Laptop and for back-up of data on the Laptop;
- Before analyzing any data from the encrypted USB device, check the data on the PWP-ART Video Laptop to ensure that there is no PII. If there is PII present, report this to the CDC Project Officer as described below.
- If PII is present, delete the PII before analyzing data.
- Complete HHS’s Security Awareness Training module before processing data and on an annual basis thereafter, as required by CDC policies.
  Link (<http://www.hhs.gov/ocio/securityprivacy/awarenesstraining/awarenesstraining.html> )
- Keep SI data out of sight when visitors are present;
- Only access SI necessary to perform job functions (i.e., need to know);
- Protect HHS information assets (HHS assets include but are not limited to hardware, software, and federal records) from unauthorized access, use, modification, destruction, theft, or disclosure and shall treat such assets in accordance with any information handling policies;
- Within 1 hour of discovery of a known or suspected security breach (lost or stolen SI; known or suspected security incidents; known or suspected information security policy violations or compromises; or suspicious activity), report to the CDC Project Officer (Contracting Officer’s Representative) who will then report the incident to the NCHHSTP ISSO. Known or suspected security incidents involve the actual or potential loss of control or compromise, whether intentional or unintentional, of SI maintained or in possession of contractors and third parties on behalf of CDC.

I shall not:

- Circumvent security safeguards including violating security policies or procedures or reconfigure systems except as authorized (i.e., violation of least privilege);
- Use another person’s account, identity, or password;
- Exceed authorized access to Share or disclose SI except as authorized;
- Store SI in public folders or other insecure physical or electronic storage locations;
- Transport, transmit or download SI unless such action is explicitly permitted by the manager or owner of such information and appropriate safeguards are in place per CDC policies concerning SI;
- Use SI for anything other than the purpose for which it has been authorized;
- Use sensitive CDC data for private gain or to misrepresent myself or CDC or any other unauthorized purpose;
- Transfer SI to **personal** mobile devices such as laptops, universal serial bus (USB) drives, or on remote/home systems;
- Knowingly or willingly conceal, remove, mutilate, obliterate, falsify, or destroy information for personal use by myself or others;
- Connect the PWP-ART Video Laptop to a server, network, or the internet either through direct or remote connection (i.e., wireless, modem);
- Load unapproved software from unauthorized sources on the PWP-ART Video Laptop;
- Use the PWP-ART Video Laptop without the following protections engaged before accessing sensitive PWP-ART Video study information:
  - Antivirus software with the latest updates;
  - A time-out function that requires re-authentication after no more than 30 minutes of inactivity; and
  - Approved encryption to protect SI stored on the PWP-ART Laptop and CDC issued USB drives.

The following are prohibited actions on the PWP-ART Video Laptop:

- Unethical or illegal conduct;
- Utilizing peer-to-peer software;

Rules for SI Applicable to All Users

Storage of SI

All SI should be stored within a CDC issued encrypted USB device or on the encrypted PWP-ART Video Laptop and stored in an area with limited access (behind a locked door, drawer, or cabinet), an access controlled electronic environment (keycard access), or under the physical control of an authorized individual. SI will not be stored on paper.

Backup of SI

All PWP-ART Video study data stored on the laptop will be backed up weekly to a separate CDC issued encrypted USB device only. Weekly backups will be maintained for at least two weeks, after which they can be deleted from the USB device. The Backup USB device will be larger than 4GB and will be coordinated with the program for delivery and issue.

Transferring SI

SI may be transferred from the beta-test clinics to CDC issued encrypted USB device and mailed to [name] only. SI will not be emailed or otherwise electronically transmitted to or from any source to the PWP-ART Video Laptop.

SI Disposal and Destruction Requirements and Methods

When no longer required, SI recorded on the CDC issued encrypted USB or PWP-ART Video Laptop will be destroyed by using an approved electronic wiping software, such as BC Wipe, degaussing or physically destroyed beyond use.

**Appendix 2: Observation Protocol**

**Waiting Room Observation Protocol**

Scheduling: Systematic observations will be conducted within the first 3 months of the beta-test period to increase the likelihood that the patients being observed are seeing the video for the first time.

Checking in: At the beginning of the shift, observer will check in with the clinic manager, determine which video playback option is being used (i.e., continuous play, 10-minute interval between cycles, 20-minute interval), determine which waiting room seats do **not** offer a clear (unobstructed) view of a video monitor, and find a seat to begin the observation.

Finding a spot for the observation: Observer will find an open seat where he/she will be able to watch patients’ reactions from the most unobtrusive location possible. The patients should not be behind the observer. The observer may change positions if his/her position is not working well.

All data will be entered on a tablet using a Survey Monkey data collection instrument. Each assessment will have four sections:

1. **Initial waiting room conditions**
2. **Systematic observation of all waiting room patients during one video cycle**
3. **Systematic observation of select waiting room patients during the next video cycle**
4. **Summary comments**

The observer will complete one assessment for every two cycles of the video. The observer will continue to complete the assessments until he/she has completed an 8-hour shift (6-8 assessments).

**1. Initial waiting room conditions**

Survey Monkey will stamp the date and time automatically. The other variables collected in this section include:

- Clinic where observations are being done
- Video version (English only/ English with Spanish Subtitles)
- Audibility (i.e. can video be heard throughout the waiting room)
- Number of monitors playing video in waiting room
- General conditions of waiting room that would impact patients’ engagement with video

**2. Systematic observation of waiting room patients**

Observer will begin this observation at the beginning of the video (i.e. video Opening shots and title) and will continue this observation through each segment of stories or animation in the video for one full cycle of the video. The observer will concentrate on patients who were not present during the previous video cycle. The observer will look around the room going from patient to patient, covering all patients that can be seen from his/her vantage point, to observe their reactions. The main objective of this section is to note any points in the video that seemed to hold patients’ attention, not hold attention, or elicit a positive or negative reaction such as laughter, discussion, or disengagement with the video. Patients who are multi-tasking while watching the video will be considered to be watching the video. Observer will use the time during the credits to note additional general observations for this cycle.

The variables collected in this section include:

- Number of patients by apparent age
- Number of patients by apparent race/ethnicity
- Number of patients by apparent gender
- Number of patients who have a clear view of a video monitor
- Number of patients in the waiting room that the observer can see (to measure engagement with video)
- Number of patients in the waiting room who were present for the previous cycle.
- General observations about engagement with all video segments for all patients for this cycle

**3. Systematic observation of select waiting room patients**

Observer will randomly choose four patients who have a clear view of the video, attempting to get a diverse sample regarding age, gender, and race/ethnicity. Patients who were not present in the previous cycle should be chosen, unless there are fewer than four patients in the waiting room who were not present during the previous cycle. If one or more of the four patients was present for the previous cycle, note this on the Survey Monkey instrument.

The observer will watch these four patients for one video cycle. Observer will begin this observation at the beginning of the video (i.e., Opening) and will continue this observation through each segment of stories or animation in the video for one full cycle of the video. The observer will record all reactions and behaviors that occur during each segment. For example, a patient may begin watching the video, have a negative reaction, and stop watching the video during a segment. If a patient is absent during one or more segments of the video during the cycle, the observer will check the “N/P” box for that patient’s reactions for those segments (e.g., if the patient leaves in the middle of a story, the observer will mark what occurred for that patient up until the time he or she leaves, and enter N/P for the rest of his or her segments). If there are fewer than 4 people in the waiting room to observe initially, the observer will enter N/P for the missing patients’ segments. However, if one or more patients subsequently enter the waiting room during this cycle, the observer should begin recording these patients.

Replacements: If one or more replacements are needed, the observer will try to match the replacement demographics in terms of gender, race/ethnicity, and age (in that order). The observer should try to identify potential replacements at the beginning of the cycle in case they are needed. If any of the initial 4 patients being observed leaves, the observer will begin observing a replacement patient (and will add the replacement’s demographics to the instrument). The replacements will be numbered in the order in which they occur from 1 to 4. The observer should take care to remember which patient is which (e.g. choose #1 and go clockwise to #4). If one of the original patients comes back, the observer will stop watching the replacement at that point and go back to watching the original patient. The observer will mark N/P for any segments for which either a replacement or an original patient are not present.

The observer will use the time during the credits to note additional general observations for the cycle. The main point of this section is to note *in detail* any points in the video that seemed to hold attention, not hold attention, or elicit a particular reaction such as laughter, discussion, or disengagement with the video specifically for the patients observed.

If any patient notices appears uncomfortable, the observer should not choose them as an observation subject or should stop observing them immediately (and begin observing a replacement) if the observation has already begun. If any patients appear to be uncomfortable, the observer should record the event in summary comments.

The variables collected in this section include:

- Apparent age of each patient
- Apparent race/ethnicity of each patient
- Apparent gender of each patient
- The duration of engagement with video for each video segment
- Reactions and watching behaviors of patient during each video segment
- Information relative to engagement of the patients for this cycle

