***Sampling, including sample size and statistical power:***

The sample for the systematic observation will be a convenience sample of all patients who are present in the waiting room during the 1 day of observation at each facility. A maximum of 8 observational assessments will be done at each facility (32 total assessments). Each observational assessment will consist of systematic observation of all waiting room patients during one video cycle and systematic observation of four waiting room patients during the next video cycle. The four patients will be chosen randomly among patients who have a clear view of the video with the intent of obtaining diversity regarding age, gender, and race/ethnicity. See Appendix 2 for the observation protocol for additional details. The unit of analysis will be the individual patients. We do not expect to revise the sampling estimates for the study.

The sample for the patient medical record data will include all HIV-positive clinic patients and their records during the historical comparison period and the intervention period. Simplified sample size calculations were performed for rejecting the null hypothesis of equality in the proportions of successes for a specific outcome, assuming equal numbers of patients in each period. These calculations correspond to an analysis using Fisher’s exact test with a two-sided significance level of α = 5%.

For the primary outcome of medication adherence (achieving viral load suppression at 6 months), if the true proportions of successes for the two periods are 70% and 77% (historical comparison to intervention, 7% absolute improvement, 10% relative improvement), then sample sizes of 650 patients prescribed ART per period will be required to have 80% power to reject this null hypothesis. Allowing for an annual attrition rate of 25%, then sample sizes of 1157 patients per period will be required to have 80% power to reject this null hypothesis.

For the secondary outcome of retention in care at 3-7 months of follow-up, if the true proportions of successes for the two periods are 75% and 82% (historical comparison to intervention, 7% absolute improvement, 9% relative improvement), then sample sizes of 566 patients per period will be required to have 80% power to reject this null hypothesis. Allowing for an annual attrition rate of 25%, then sample sizes of 1008 patients per period will be required to have 80% power to reject this null hypothesis.

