***Intervention or treatment:***

The intervention that will be tested will be a short “soap opera” style waiting room video with three interwoven vignettes that incorporate key prevention messages aimed at increasing early treatment initiation, treatment adherence, retention in care, and partner protection for people with HIV. The video will contain characters who represent various populations, including women, gay men, heterosexuals, African-Americans, and Latinos. The video will also include a short animation focusing on treatment adherence. The video is meant to play in the waiting room throughout the day for 10 months. Optimally, the video will play on a continuous loop. Some facilities may need short pauses between video replays based on their local circumstances. If this need arises, the pause interval will be discussed with and approved by CDC.

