***Bias in data collection, measurement, and analysis:***

Biases with regard to the observation: Observation bias could affect the validity of the data. This bias will be minimized by having only one observer and training him to conduct the observation in a systematic fashion using an online instrument to guide the data collection, which will enhance observer consistency. Bias is also minimized by the data collection instrument requiring a low level of observer inference or interpretation of observed behaviors. In a waiting room patients are a collection of individuals and not participants in an interactive group, so the presence of a non-interacting observer should not influence patient behavior. Bias from expectancy effects will be offset by checking for correspondence between observed disengagement and medical outcomes addressed during segments when many patients were disengaged. There could be bias due to an inability of the observer to correctly recognize the HIV-positive patient characteristics (race/ethnicity, age, gender) or whether or not patients are truly engaged with the video or merely looking in the direction of the video screen. To a certain extent, this bias is inherent in the study design, and would be difficult to avoid without approaching the patients. Measurement bias could affect the generalizability of the data. Observations are limited to once per facility. Bias is minimized by conducting observations for eight hours, for a total of 24 assessments and an estimated 192 to 336 patients observed across all three facilities. The eight-hour observation period will minimize time-of-day bias but will be affected by day-of-week and month-of-year differences. Observations will be conducted during the first two months of the intervention period to minimize potential bias from previous exposure to the video.

Biases with regard to the patient medical data:

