### 2f. How many of these patients were present for any portion of the previous video cycle?

|  |
| --- |

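### The four select patients are called randomly chosen, but the observer who rates them picks them by eye, so selection can follow visible engagement whenever too few new arrivals are present

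*Protocol*

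**What the plan says.** The selection rule appears twice. Appendix 2, section 3 (select waiting room patients) states: "Observer will randomly choose four patients who have a clear view of the video, attempting to get a diverse sample regarding age, gender, and race/ethnicity". The Sampling section of the main text repeats it: "The four patients will be chosen randomly among patients who have a clear view of the video with the intent of obtaining diversity". Neither place gives a list, seat number, random number or stratum.

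Other text bears on the choice:

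- **New-arrival preference** (Appendix 2, section 3): "Patients who were not present in the previous cycle should be chosen, unless there are fewer than four patients in the waiting room", where the exception counts only patients who were not there for the previous cycle. Item 3a of the instrument records whether each selected patient had been present.
- **Replacements** (same section): picked to resemble the departed patient, with gender taking priority over race/ethnicity and that over age. Candidates are earmarked early: "The observer should try to identify potential replacements at the beginning of the cycle in case they are needed".
- **Discomfort rule** (same section): anyone who appears uncomfortable is not chosen or is dropped.
- **Preceding cycle** (Appendix 2, section 2): the observer watches every visible person in turn for reactions.
- **Bias section**, on observation bias: "This bias will be minimized by having only one observer and training him to conduct the observation in a systematic fashion".

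**The concern.** A draw can be both random and diverse only if it is stratified and the strata and mechanism are stated. Without them, the instruction describes a judgement sample under the name of a random one. This is not detail that a statistical analysis plan would supply, because Appendix 2 is the observer's working instruction.

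The person choosing is also the person rating, and has just spent one video cycle watching how the room reacts. If the candidates include people already watched, the choice can lean toward those facing the screen, or toward those who are not. A single observer makes recording consistent, but also makes any such preference systematic across the three sites.

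At stake is the select-patient half of each assessment. It is the only source of patient-level duration and reaction data by segment. The Data analysis plan evaluates that duration quantitatively and uses this half to locate disengaging scenes. The data also bear on Hypothesis 1, that patients pay attention and react favourably.

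**Working it through.** The plan states no figure for this point, so there is none to reproduce. The check has two parts.

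**1. Does the new-arrival preference prevent selection on engagement already seen?**

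When four or more new arrivals are available, largely yes: the people just watched are not eligible. The question is how often that happens. The Intervention section gives the preferred playback: "Optimally, the video will play on a continuous loop". The only place that spells out what counts as earlier presence is instrument item 2f: "How many of these patients were present for any portion of the previous video cycle". Under a continuous loop, the next Opening follows directly on the previous cycle. Nearly everyone seated at that moment will have been there for some portion of it, so fewer than four new arrivals is a likely state. With the 10- or 20-minute pauses that Appendix 2 also allows, the preference works better. When it lapses, the document leaves the choice to the observer.

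**2. How large could the effect be?**

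Inputs from the protocol:

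- Four patients are selected per assessment.
- The Bias section gives 24 assessments and 192 to 336 people observed. (The Sampling section's total of 32 does not match 3 sites × 8 = 24; that is a separate matter, and 24 is used here.)
- People observed per assessment: 192/24 = 8 and 336/24 = 14.

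These are people observed, not candidates. Candidates need a clear view and should preferably be new arrivals, so the eligible pool is probably smaller. The protocol does not state it, so a range from 4 to 14 is shown.

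Assumptions, none of them in the documents: 50% of eligible patients are engaged, and an engaged patient is *w* = 1.5 or 2 times as likely to be picked at each draw. With *a* engaged and *b* non-engaged patients still available,

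P(next pick is engaged) = *w·a* / (*w·a* + *b*).

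Example, first pick with *a* = *b* = 4: at *w* = 1.5, 6/(6 + 4) = 0.60; at *w* = 2, 8/(8 + 4) = 0.67. Later picks are pulled back as the engaged patients are used up. Averaging over all four picks and over the binomial number engaged gives the expected shift in the engaged share, in percentage points:

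| Eligible pool | *w* = 1 (random) | *w* = 1.5 | *w* = 2 |
|---|---|---|---|
| 4 | 0 | 0 | 0 |
| 5 | 0 | 3.2 | 5.2 |
| 6 | 0 | 4.8 | 7.9 |
| 8 | 0 | 6.4 | 10.8 |
| 14 | 0 | 8.1 | 13.7 |

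If disengaged patients are favoured by the same ratios, the shifts have the same size with the opposite sign. A true random draw gives no shift at any pool size. More assessments would not remove a shift of this kind.

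**The case against.** The case on the other side has weight, and much of it stands.

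- **The choice is not unconstrained.** A reader might infer that nothing stops the observer from choosing among people already watched. The new-arrival preference does so when four new arrivals are present, and item 3a logs the exceptions. The concern is confined to the fallback.
- **Knowledge of the hypothesis is not documented.** A reader might assume that the observer knows it. The Training section mentions only the observation protocol, the instrument and conduct toward patients. The concern does not need that assumption.
- **The upper figures may not apply.** Pools of 8 to 14 treat everyone observed as eligible. With exactly four eligible, there is no choice to bias.
- **No pooled proportion is defined.** With 24 × 4 = 96 select patients, the standard error of a 50% share is √(0.25/96) = 5.1 points, and a reader might infer that Hypothesis 1 is biased by more than its sampling error. The Data analysis plan sets no engaged share, test or threshold for Hypothesis 1. Its one quantitative item is duration per segment, so the comparison lacks a planned statistic.
- **Seeking diversity is not itself a flaw.** Objective 1 asks about responses across ages, genders and race/ethnicities, and the approach is described as developmental. One could compute that giving half the picks to a group forming 10% of the room, with a 20-point engagement gap, moves a pooled share by (0.50 − 0.10) × 20 = 8 points. But 10% of a room of 8 to 14 is 0.8 to 1.4 people, so two such picks would not be available on average.
- **Representativeness is not claimed for the whole.** The Sampling section says "The sample for the systematic observation will be a convenience sample of all patients who are present in the waiting room", and the first cycle of each assessment covers everyone visible.

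None of this supplies a random mechanism. Neither the Bias section nor the Limitations section discusses how the four are picked.

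**Conclusion.** The point holds in a limited form. The protocol calls the choice of the four patients random in two places, but what it describes is a judgement choice by the person who then rates them, with judgement-matched replacements. The new-arrival preference is a real but partial guard, and it is likely to lapse under the preferred continuous loop. In that state, selection can follow visible engagement in either direction.

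The size cannot be derived from the documents. Under the assumed picking ratios of 1.5 to 2 and 50% true engagement, it is 0 points with four eligible, about 3 to 8 with five or six, and about 6 to 14 with eight to fourteen. The documents do not show that such a preference will occur.

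The consequence is confined to the select-patient duration and reaction data, and so to Hypothesis 1 and scene refinement. Hypotheses 2 to 5, which rest on medical records, are not touched.

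**What to change.** Either of two changes would do.

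**Make the draw random.** At check-in the observer already notes which seats lack a clear view. At the same time, number the seats that have a clear view of the video and that the observer can see unobtrusively. Preload on the tablet a separate random seat order for each assessment. Before the Opening, take the first four occupied seats on the list whose occupants meet the existing new-arrival and discomfort rules, keeping the present fallback when fewer than four are new. Take replacements in list order. If diversity is wanted, name the apparent demographic groups beforehand and draw within them from the same list.

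Do not weight the results back to items 2c to 2e. Those items are separate marginal counts of the room in the first cycle, whereas the select patients are watched in the next cycle and are preferably people who were not there before.

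**Or name the sample for what it is.** Delete *randomly* in the Sampling section and in Appendix 2, call the four a purposive sample, and report their results descriptively rather than as a test of Hypothesis 1.

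The first option costs a paragraph in Appendix 2, a matching edit in the Sampling section and a short seat list prepared for each site; a given set of four may also be less diverse. The second costs only the wording and the stronger claim. Neither needs more staff, visits or patients.
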